
#### Study size

The sample size of 38 participants per year of surgery (2013–2019) was calculated based on the expected 0.1 % prevalence of bariatric surgery with a 95 % confidence interval and a 1 %, margin of error totaling 266 participants.

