### Phase 1: cross-sectional study

#### Study design

This is a cross-sectional study to be conducted with patients who underwent bariatric surgery until 2020, seeking to identify the main differences between patients with weight maintenance, with expected weight gain and progressive weight regain, and thus refine the hypotheses of the study's Phase 2.

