#### Participants

Participants will be included in the sample: adults aged ≥18 who underwent sleeve gastrectomy or Roux-en-Y Gastric Bypass, after at least two years. The sample considers patients with ‘weight maintenance’, those who keep the minimum weight achieved after bariatric surgery (nadir); patients with ‘expected weight gain’, a recovery <20 % of weight lost in the long term, according to the Brazilian Society of Bariatric and Metabolic Surgery (SBCBM) [27] and patients with ‘progressive weight regain’ those who recovery > 20 % of in the long term.

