#### Statistical methods

All variables will be described using the Kolmogorov-Smirnov test to verify the normal distribution of data. For sociodemographic and other questions, absolute and relative frequencies will be calculated for categorical variables and means whereas standard deviations will be estimated for continuous variables. Pearson's and Spearman's correlation coefficients will be used to identify the correlation between the study variables. The theoretical behavior expected from the scales will be confirmed by linear regression analysis. The level of significance will be 5 % (*p* < 0.05) in all tests and no adjustments for multiple comparisons will be considered, in accordance with the exploratory nature of Phase 1.

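### Phase 1's 266 participants are justified by a prevalence of bariatric surgery that an all-surgery sample cannot estimate, so the stated 1% margin applies to nothing Phase 1 reports

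*Protocol article*

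**What the plan says.** In the protocol article, the Phase 1 Study size section opens: "The sample size of 38 participants per year of surgery (2013–2019) was calculated based on the expected". The value it assumes is for the following quantity: "0.1 % prevalence of bariatric surgery". The other inputs are 95% confidence and a margin of 1 percentage point, and the total over the seven surgery years is given as 266.

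The Phase 1 Participants section admits only "adults aged ≥18 who underwent sleeve gastrectomy or Roux-en-Y Gastric Bypass, after at least two years". It defines three groups by weight course after surgery.

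The Phase 1 Study design section gives the purpose as "seeking to identify the main differences between patients with weight maintenance, with expected weight gain and progressive weight regain", so that the Phase 2 hypotheses can be refined.

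The Phase 1 Statistical methods section lists a normality test, frequencies, means and standard deviations. It then says that "Pearson's and Spearman's correlation coefficients will be used to identify the correlation between the study variables", and adds linear regression to confirm that the scales behave as theory expects. Tests are at 5% without multiplicity adjustment, because Phase 1 is declared exploratory.

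**The concern.** A precision-based sample size should be tied to a quantity that the study will estimate. The quantity used here is how common bariatric surgery is. In a sample made up only of people who have had the operation, that proportion is 100% by design, and no Phase 1 output reports it. A margin of 1 percentage point around an assumed 0.1% would also say very little.

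A reader of the article would take from it that 266 participants deliver 1% precision on something. They do not, and what they do deliver for the three-group aim is not stated.

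There is a smaller mismatch alongside. The aim is to find differences between three weight-course groups, but the listed methods do not name a comparison of those groups.

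**Working it through.** **1. Reproduce the plan's figure.** The inputs from the Phase 1 Study size section are p = 0.001, margin d = 0.01, 95% confidence (z = 1.96) and seven surgery years (2013 to 2019).

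n = z² p(1 − p) / d² = 1.96² × 0.001 × 0.999 / 0.01² = 38.4 per year.

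Rounded to the nearest whole number this is 38, and 38 × 7 = 266, exactly as stated. Strict rounding up would give 39 and 273, a difference of no importance.

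**2. Test the basis.**
- The margin is 0.01 / 0.001 = 10 times the assumed prevalence. The implied interval is 0.1% ± 1.0%, or −0.9% to 1.1%.
- With n = 38 and p = 0.001 the expected number of cases is 38 × 0.001 = 0.038, so the normal approximation behind the formula does not apply. With 0 cases in 38, the exact two-sided 95% upper limit is 1 − 0.025^(1/38) = 9.3%. The 1-point precision would not be reached even for the formula's own target.
- Under the inclusion criteria the proportion with surgery is fixed at 100%, so there is nothing to estimate.
- For a proportion that Phase 1 could report, such as the share with progressive regain, the article gives no expected value. Assuming 10% to 50%, a 1-point margin would need 1.96² × 0.10 × 0.90 / 0.01² ≈ 3,458 to 1.96² × 0.25 / 0.01² = 9,604 participants. The small figure of 38 arises only because a near-zero p was entered with a wide absolute margin.

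**3. What 266 does give.**
- Proportion near 50%: 1.96 × √(0.25 / 266) = ±6.0 points. For a proportion near 10%: 1.96 × √(0.09 / 266) = ±3.6 points.
- Correlation, two-sided 5%, 80% power, Fisher z: tanh(2.80 / √263) = 0.17.
- Three-group one-way ANOVA at 5%, N = 266, groups assumed equal, no covariates: 80% power at f ≈ 0.19. Power is 29% at f = 0.10, 84% at f = 0.20 and 96% at f = 0.25.
- Unequal groups: the article gives no group shares, so this is a range under assumption. The standardised difference detectable between two groups with 80% power is 0.42 for 89 against 89. It is 0.55 for 40 against 80, and 0.63 for 27 against 80.

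**4. Aim against methods.** The aim is differences between three groups. Of the methods listed, the descriptives are not said to be by group, the correlations concern the study variables generally, and the regression has a different stated purpose. None names the three-group contrast.

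**The case against.** The best defence has four parts.

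- **The calculation is right.** This stands. A reader might infer that 38 or 266 is miscalculated, but the stated inputs produce both figures. The fault is in the choice of target.
- **The size may be adequate.** This also stands. A reader might infer that Phase 1 is too small. The documents give no effect size or group shares from which that could be shown, and 266 is a usable number for moderate differences if the groups are reasonably balanced.
- **A condensed article need not name every test.** This stands in large part. A reader might infer that the group differences will never be produced. The text does not support that. A fuller plan may specify the comparison, weight history is among the data collected and so falls within the correlations, and the methods refer to multiple comparisons without naming any. What remains is a mismatch between the stated aim and the stated methods.
- **Little depends on it.** Phase 1 is exploratory. Phase 2 has its own sample size calculation, recruits beyond Phase 1 respondents, and admits any weight increase from nadir instead of using the Phase 1 groups. This limits the weight of the point.

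None of this rescues the stated justification. It is given in the article itself, so it is not a detail left to another document, and no other section supplies a target that fits.

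**Conclusion.** The point holds as a mis-targeted justification. The 266 follows correctly from its inputs, but those inputs describe a prevalence that Phase 1 cannot estimate, with a margin ten times the assumed value. The stated 1% precision therefore attaches to nothing Phase 1 will report. For a proportion near 50% the real half-width is about 6.0 points.

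The figure of f ≈ 0.19 is a power threshold and not a precision. It rests on two assumptions that the article does not make: equal group sizes and no adjustment. Sensitivity falls if one group is small.

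The missing group comparison is secondary, and is a matter of aligning two sections. The randomised comparison in Phase 2 does not depend on 266. The correction is worth making because it costs almost nothing, but it does not threaten the trial.

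**What to change.** 1. In the Phase 1 Study size section, delete the prevalence rationale and the 1% margin. Keep 266 as the chosen size, with 38 per surgery year as the allocation.
2. State what it provides: about ±6.0 points (95% CI) for a proportion near 50%, and 80% power for a correlation of about 0.17. Add 80% power for a three-group effect f of about 0.19, explicitly conditional on equal groups and an unadjusted analysis. Say that sensitivity is lower if the groups are unequal, preferably with the group shares the investigators expect.
3. In the Phase 1 Statistical methods section, name a comparison of each scale across the three weight groups. ANOVA, or linear regression on group with surgery year as a covariate, would be a reasonable choice. If a fuller plan already specifies this, a sentence pointing to it is enough.

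The cost is wording and one standard analysis. No further participants or data items are needed.

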#### Statistical methods

All variables will be described using the Kolmogorov-Smirnov test to verify the normal distribution of data. For sociodemographic and other questions, absolute and relative frequencies will be calculated for categorical variables and means whereas standard deviations will be estimated for continuous variables. Pearson's and Spearman's correlation coefficients will be used to identify the correlation between the study variables. The theoretical behavior expected from the scales will be confirmed by linear regression analysis. The level of significance will be 5 % (*p* < 0.05) in all tests and no adjustments for multiple comparisons will be considered, in accordance with the exploratory nature of Phase 1.

### Phase 2: clinical trial

#### Trial design

This is a randomized controlled clinical trial of mixed methods with random allocation in three groups: G1 (MBHP + workshops); G2 (ABCT + workshops); and G3 (workshops), with patients who underwent gastroplasty and regained weight from the clinic already mentioned.

#### Eligibility criteria

Samples will consist of adults who underwent any type of bariatric surgery and had any progressive weight gain. Since the literature has no conceptual definition of weight regain [43], and taking into account the subjective nature of the issues involved in weight regain, knowing that, for some people, regaining weight (as little as possible) can be a devastating experience that contributes to a negative spiral in weight control [10], the adopted criterion will consider any weight increase from nadir. Those who by chance use medications for weight loss, who are pregnant or intend to get pregnant in the next eight months, who have substance abuse disorder (alcohol or drugs), severe depression, schizophrenia or psychotic disorders, who use drugs that cause cognitive loss of attention and concentration, and who have previously practiced mindfulness, meditation, yoga, or similar practices in the last six months will be excluded from the study. Patients diagnosed with severe depression by HADS scale who are not undergoing treatment will be referred to the nearest mental health service facility for evaluation and follow-up.

#### Interventions

The interventions described below will occur in an interactive online format (synchronous). Fig. 1 shows the flow diagram. Instructors of MBHP and ABCT protocols will be those health professionals (psychologist, physician or pharmacist), experienced in management of patients with severe obesity, certified by mindfulness institutions internationally validated, and with over two years of experience in facilitating groups of said protocols.

**Fig. 1 fig0001:**
[figure not shown]
Diagram of planned study flow. Abbreviations: MBHP, Mindfulness-Based Health Promotion; ABCT, Attachment-Based Compassion Therapy.

##### Workshops

All participants will be invited to two online workshops (synchronous) of two hours each, with a 30-day interval between each one. The themes and methodology of the workshops were adapted from the Instruction of the Brazilian Ministry of Health [44], which proposes several actions of food and nutrition for group work. The first meeting will work on the themes “who are we?”, “what is health for you?” and “the balance of choices”, in order to create a reflective environment and work on intrinsic motivation; the second meeting will focus on the theme “planning my food”. All participants will be invited to bring a pen and paper to write down their own reflections and plans during the workshops.

##### Mindfulness-based health promotion (+ workshops)

MBHP is a program designed by Mente Aberta Center to address universal human vulnerabilities, not focusing on any specific health condition, within the context of health promotion [45]. The program is structured and developed over eight weekly sessions, in which participants meet for an average of two hours to experience technical and conceptual learning about mindfulness (Table 1). They are also given suggestions for activities to do at home, daily. The main techniques used are practices of mindful breathing, body scan, mindful walking, and mindful movements [45].

**Table 1 tbl0001:** Protocols for Mindfulness-Based Health Promotion (MBHP) and Attachment-Based Compassion Therapy (ABCT) interventions.

Session	MBHP	ABCT
1	**What is mindfulness**	**Preparation for compassion**
	*Formal practice:*	*Formal practice:*
	- Raisin meditation	- Compassionate breathing
	- Body scan meditation	- Compassionate body scanning
2	**Mindfulness in breathing**	**Discovering the compassionate world itself**
	*Formal practice:*	*Formal practice:*
	- Mindful breathing	- The figure of affection: connecting with basic affection
	- Body scan meditation	- Development of a safe place
		- Compassionate action
		- Identification of the secure attachment figure
3	**Mindfulness in the body (part I)**	**Development of the compassionate world itself**
	*Formal practice:*	*Formal practice:*
	- Mindful walking	- Development of the secure attachment figure
	- Mindful breathing	- Development of a compassionate voice
4	**Mindfulness in the body (part II)**	**Understanding our relationships with compassion**
	*Formal practice:*	*Formal practice:*
	- Mindful movements	- Awareness of attachment styles
	- Mindfulness in breathing, sensations, sounds, and thoughts	- Ability to receive affection: friend, indifferent person, enemy
	- 3 min breathing in pairs	
	- Mindful walking	
5	**Mindfulness and acceptance**	**Working on ourselves**
	*Formal practice:*	*Formal practice:*
	- Mindful movements	- Show affection to friends and indifferent people
	- Mindful thinking	- Show affection to yourself
	- 3 min breathing in pairs	- Reconcile with parents
		- Three positive and negative aspects of parents
6	**Silence**	**Advanced compassion (I); forgiveness**
	*Formal practice:*	*Formal practice:*
	- Mindful movements	- Forgive yourself
	- Body scan meditation	- Ask others for forgiveness
	- Mindful breathing	- Forgive others and show compassion to enemies
	- Mindful walking	- Show forgiveness for the pain caused by a loved one
		- Recapitulation
7	**Compassion**	**Advanced compassion (II): becoming your own attachment figure and dealing with difficult relationships**
	*Formal practice:*	*Formal practice:*
	- Loving kindness (for yourself and others)	-Working with envy
	- Mindful breathing	-Becoming your own attachment figure
	- Mindful movements	- Dealing with difficult relationships
8	**Mindfulness for life**	**Beyond compassion: equanimity**
	*Formal practice:*	*Formal practice:*
	- Loving kindness (for yourself and others)	- Equanimity I: we are all equal
	- Mindful poetry	- Equanimity II: the illusion of categories
		- Equanimity III: showing the world the gratitude we were unable to return

##### Attachment-based compassion therapy (+ workshops)

ABCT is a program based on attachment styles, a psychoanalytical concept which describes the relationship children develop with their parents, and which will influence the interpersonal relationships and self-image they will eventually develop. [19]. Participants meet for two or two and half hours at each meeting for eight weeks. ABCT teaches formal (seated meditation) and informal (during daily life) self-compassion (Table 1). Experimental exercises and discussion periods conducted in each session, together with homework, help participants learn how to be kind to themselves [19].

#### Outcomes

The primary outcome will be a change in the eating behavior (TFEQ-21, Rep (eat)-Q, and BES) at all steps. Secondary outcomes will be improved quality of life (M-A QoLQII), increased satisfaction with body image and reduced distortion (BSSA), better weight management (maintenance or weight reduction), increased frequency of physical activity, and monitoring with the surgery team. The explicative variables will be the level of mindfulness (MAAS), self-compassion (SCS-SF), anxiety (HADS), and attachment style (ECR-R).

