#### Measurements

All data will be collected by patient report using an electronic online form (SurveyMonkey®) containing closed and open questions distributed among a socio-demographic survey and validated scales in Portuguese.-Sociodemographic and others: An instrument containing, age, gender, marital status, associated diseases, lifestyle habits, and weight evolution before and after surgery and other questions related to objectives, such as questions about adherence to post-surgical follow-up consultations, nutritional recommendations and attendance to support groups, psychological and/or psychiatric treatment and physical activity.-The 21-item Three-Factor Eating Questionnaire (TFEQ-R21): This scale has 21 items that assess three aspects of eating behavior: cognitive restriction, emotional eating, and uncontrolled eating. Higher scores indicate greater cognitive restraint, uncontrolled eating or emotional eating [28,29].-Repetitive Eating Questionnaire [Rep(eat)-Q]: This is a 12-item questionnaire to assess grazing, with two graze subtypes: repetitive eating and compulsive grazing. An overall average of the 12 items will be calculated. The scores for each domain will be calculated as an average of all items in each domain. Higher scores indicate more presence of grazing feeding behavior [30].-Binge Eating Scale (BES): This is a scale of 16 items and 62 statements that was built in three stages: characteristics of binge eating, severity of each characteristic, and an external criterion of severity (frequency, amount of food, and degree of emotion involved in an episode). Each statement corresponds to a number of points from 0 to 3, ranging from absence “0″ to maximum severity “3″ of binge eating. The overall score will be categorized as follows: non-binging ≤ 17 points, moderate binging 18 to 26 points, and severe binging ≥ 27 points. [31,32].--Moorehead-Ardelt Quality of Life Questionnaire II (M-A QoLQII): This is a self-administered questionnaire which addresses quality of life, updated from a part of the Bariatric Analysis and Reporting Outcome System. It contains six questions with a 10-point Likert scale that assesses the following domains: general self-esteem, physical activity, social contacts, job satisfaction, pleasure related to sexuality, and focus on eating behavior. The scores for each item and the overall average of the 6 items will be used to generate an overall quality of life score. Higher scores indicate better self-perception of quality of life. [33].-Brazilian Silhouette Scales for Adults (BSSA): This scale has 15 images for each gender, with a white figure centered on a black background. The adult scales include the BMI averages corresponding to each figure ranging from 12.5 to 47.5 kg m^-12^, with a constant difference of 2.5 points [34]. This scale will be used to assess body image distortion, when the participant indicates which image, they resemble the most (considered distorted body image when they choose a silhouette different from their current BMI) and to assess body image dissatisfaction when the participant responds what image would they like their bodies to be. Dissatisfaction with body image will be analyzed based on the disagreement between the current silhouette and what they would like to look like, and the participants will be classified as satisfied and dissatisfied. Then, subjects with body dissatisfaction will be dichotomized into those who wanted to increase their body size (dissatisfaction due to thinness) and those who wanted to reduce their body size (dissatisfaction due to excess weight).-Mindful Attention Awareness Scale (MAAS): The MAAS is an instrument that assesses mindfulness and consciousness levels according to time. This 15-item scale indicates how often the participants experienced each of the situations described in the items. Higher scores reflect higher levels of dispositional attention [35,36].-Self-Compassion Scale – Short Form (SCS-SF): The brief 12-item SCS-SF assesses the feeling of compassion for the self in dimensions of self-kindness, self-judgment, common humanity, isolation, mindfulness, and over-identification. Higher scores mean more self-compassion. [37,38].-Hospital Anxiety and Depression Scale (HADS): This 14-item scale measure signs of anxiety and depression. It has three stages for the two subscales: possible anxiety and depression disorders (8–10 points), probable anxiety and depression disorder (11–14 points), and severe disorder (15–21 points) [39,40].-Experiences in Close Relationship Scale – Reduced (ECR-R-Brazil): This 10-item scale measures adult attachment in the context of love relationships, containing two dimensions of attachment, anxiety and avoidance. Higher scores indicate higher levels of attachment-related anxiety and avoidance [41,42].

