#### Assessment

Quantitative and qualitative assessments will be performed before the intervention (T0), immediately after the intervention (T1) and at the six months follow-up (T2). Participants will respond to the same electronic form used in Phase 1 of the study at the three evaluation moments (T0, T1 and T2) and after the intervention they will be able to respond subjectively about their adherence to the sessions, frequency of performing formal practices and report if there were unexpected effects (adverse events) in periods T1 and T2 by completing another electronic form [46]. After six months of follow-up, the control group will be offered the intervention (MBHP or ABCT) considered most effective to improve eating behavior (Fig. 2).

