#### Sample size

Sample size estimates indicate that for a 30 % improvement in the primary outcome for groups G1 and G2 and 5 % for group G3 (workshop), with a 95 % bilateral confidence interval and 80 % power, each group will need at least 43 participants. Assuming that 25 % of patients would be lost to follow-up, each group would need 54 patients, with 162 participants in total.

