## Discussion

To the best of our knowledge, this RCT is the first to directly compare the effectiveness of a protocol of CBI (ABCT) with an MBI (MBHP) in bariatric patients with progressive weight regain in feeding behaviors settings. Both programs in this study were developed to meet the cultural characteristics of Latin Americans [19,45] with maximum feasibility, safety and efficacy.

The present study is made relevant given the possible consequences for both physical and emotional health in the progressive weight regain [4,10], especially since training in the MBHP and ABCT protocols may increase levels of mindfulness, self-compassion and reduce levels of anxiety, as observed in other studies [18,21], and also promote improvements in quality of life, satisfaction with body image and reduced distortion. Thus, it is believed that the reduction of negative emotions or better management skills of these emotions can improve eating behaviors, mainly with the reduction in the prevalence of grazing, binge eating, cognitive restriction, emotional eating and uncontrolled eating, all of which were previously associated with weight regain and increased psychological distress [8,11,[14], [15], [16]].

Well-being improvement can mobilize better self-care engagement, for instance increasing the frequency for both monitoring with the surgery team and physical activity. Together, all the previously mentioned aspects can contribute, in medium to long term, to a better weight management (maintenance or weight reduction) throughout life.

And finally, it was hypothesized that ABCT training could be more effective than the mindfulness program because it has lots of ‘constructive’ practices and this family of practices may aim to promote healthy interpersonal dynamics, to strengthen a commitment to ethical values, or to nurture habits of perception that lead to enhanced well-being [20]. Also, because attachment orientation may be a factor worth considering when addressing disinhibited eating, especially in the context of poor outcomes following bariatric surgery [48]. If this hypothesis is confirmed, further studies will be needed to confirm whether this can be considered another strategy with potential for adjuvant treatment of post-bariatric obesity recurrence.

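### Monitoring with the surgery team is collected by self-report from participants who know their arm, although they come from the clinic that operates; counting it from clinic records would be a cheap, minor improvement.

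*Protocol article*

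**What the plan says.** The Outcomes section of Phase 2 names as secondary outcomes "increased frequency of physical activity, and monitoring with the surgery team". The Discussion confirms that a frequency is meant and gives it a role: better well-being is expected to improve self-care, for instance by "increasing the frequency for both monitoring with the surgery team and physical activity", which is in turn expected to help weight management.

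On the source, the Measurements section of Phase 1 says "All data will be collected by patient report using an electronic online form", and the sociodemographic part of that form includes "questions about adherence to post-surgical follow-up consultations, nutritional recommendations and attendance to support groups". The Assessment section carries the form into the trial: "Participants will respond to the same electronic form used in Phase 1 of the study at the three evaluation moments". Clinic appointment or chart records are not mentioned.

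On the setting, the Trial design section describes a trial "with patients who underwent gastroplasty and regained weight from the clinic already mentioned". The Study design section says that about 8000 bariatric operations have been done at this clinic, and the Recruitment section says that its doctors and multidisciplinary team recruit, alongside its social networks. The Sample size section assumes that 25% "of patients would be lost to follow-up, each group would need 54 patients".

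The Discussion admits limits of a self-administered online questionnaire, but names memory bias only for reported weight.

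**The concern.** The eating, mood and mindfulness scales have to be self-reported. Attendance at consultations does not: it is an event that the host clinic can be expected to log. Two weaknesses follow from taking it from the form.

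- **Reporting bias.** No blinding is described, and none is possible for a participant who attends eight weekly sessions or does not. Someone who has spent eight weeks in a health programme may be readier to report good self-care than someone who had two workshops. Over-reporting that is larger in the programme arms would look like a treatment effect.
- **Missing data.** A participant who does not return the T2 form has no value for this outcome, even if the clinic knows whether that person attended. Those who leave the study may also be those who stop attending follow-up, so the loss may be informative.

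What is at stake is the interpretation of one secondary outcome, and of the self-care argument that the Discussion builds on it.

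**Working it through.** **Inputs from the protocol article.** Expected improvement 30% (G1, G2) against 5% (G3), two-sided 5% level, 80% power, 43 per group; 25% loss; 54 per group; 162 in total (Sample size section).

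**1. The plan's own figure.** The normal-approximation formula for two proportions with continuity correction, at 0.30 against 0.05, two-sided 0.05 and 80% power, gives 43 per group, as stated (36 without the correction). The 54 is 43 × 1.25 = 53.75, rounded up. The present point uses only the 54, the 162 and the 25%.

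**2. How many values remain at T2.**
- Per arm: 54 × 0.75 = 40.5.
- Whole trial: 162 × 0.75 = 121.5 with a value and 162 × 0.25 = 40.5 without, so about 40 participants are missing.

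The 25% is a planning assumption, and some of those lost by T2 may still have answered at T1.

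**3. What the missing values could hide.** The article gives no attendance rate, so one is assumed. If a share p of responders attended and 25% are missing, the rate for the whole arm lies between 0.75p and 0.75p + 0.25:
- p = 0.30: 22.5% to 47.5%.
- p = 0.50: 37.5% to 62.5%.

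The range is 25 points wide per arm in both cases. These are worst-case bounds, not expected bias.

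**4. What differential over-reporting could do (hypothetical).** Assume 40 responders per arm, equal true attendance of 40% or 50% in both arms, accurate control answers, and a reported share that is d points too high in the programme arm. For each d, the probabilities of all pairs of binomial counts for which the pooled two-proportion z-test is significant at the two-sided 5% level are summed:

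| d (points) | Trials with a significant difference |
|---|---|
| 0 | about 5% to 6% |
| 5 | about 8% |
| 10 | about 16% |
| 15 | about 29% |
| 20 | about 46% |

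At 30% true attendance the figures for 10, 15 and 20 points are about 15%, 28% and 46%, so the assumed base rate matters little. The size of d matters a great deal, and the article gives nothing from which to estimate it. The outcome is also a frequency, so a yes/no share is a simplification.

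**5. The most that precision could gain.** If records existed for all 54 per arm, the standard error would be sqrt(40.5/54) = 0.87 of its value with 40.5, a reduction of about 13%. This is an upper limit, because some participants may be followed elsewhere.

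**The case against.** The strongest case against the point has four parts.

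- **Differential bias is not shown.** The listed sessions of the two programmes contain nothing on attending surgical follow-up. All three arms get health workshops, an online interaction group and individual contact after a missed session. Over-reporting that is equal across arms would not produce the false positives above. This stands as a limit on size: unequal contact with health professionals makes some difference plausible, but its amount is unknown.
- **Form-only collection is a reading.** The statement that all data come by patient report stands under Phase 1. The Assessment section says that the same form is used in the trial, not that nothing else is, and the article condenses a fuller protocol. The fair wording is therefore that the outcome is self-reported as described.
- **Records are not complete either.** They would score follow-up obtained elsewhere as zero, and part of the recruitment runs through social networks. This also stands. A reader might infer that records would free this outcome of attrition; the article does not support that.
- **The outcome is minor.** It is the last-named secondary outcome of a feasibility trial seeking preliminary evidence, and the limitations already admit the self-administered form. This sets the severity.

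A reader might also infer that the form mixes planned follow-up with visits prompted by a problem. The article does not support this: it describes the item as adherence to follow-up consultations after surgery, and the questions themselves are not shown.

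**Conclusion.** The point holds as a minor one. As described, frequency of monitoring with the surgery team rests on self-report by participants who know their arm, and at the planned loss it would be missing at T2 for about 40 of 162. The clinic that performs the surgery is also the source of the trial patients, so a less bias-prone source is probably at hand.

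Two steps are inference: that participants are unblinded, which follows from the form of the interventions and the absence of any stated blinding, and that usable appointment records exist, which follows from the setting. The false-positive figures of about 8% to 46% depend entirely on assumed over-reporting of 5 to 20 points in one arm, and are no estimate of what will happen in this trial. The primary outcome, the sample size and the main conclusion are not affected. Nor does the point extend to the questionnaire scales, for which self-report is the proper source.

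**What to change.** Define the outcome as the number of follow-up consultations with the surgery team in the clinic's appointment records, from T0 to T1 and from T0 to T2, each with a window of equal length before T0 as baseline. Count it for every randomised patient of the clinic, whether or not forms are returned. Keep the form answer as supportive. Ask at T0 whether the participant is followed elsewhere, so that those participants can be identified without relying on later forms and analysed on self-report in a sensitivity analysis.

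The cost is a look-up in the clinic's records, a line in the consent form and one question at T0, with no extra visit or procedure. The drawback is that records miss care obtained elsewhere, so reporting bias and attrition are reduced, not removed. If records prove unusable, the form answer can stay as the measure, with the Discussion's limitation on memory bias extended to attendance.
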